### Eligibility criteria

#### Inclusion criteria

The inclusion criteria are as follows: (1) patients who have a history of hepatitis B infection or HBsAg positive for more than 6 months, and their current HBsAg and/or HBV DNA levels are still positive; (2) patients who meet the criteria for antiviral indications in the “Asian-Pacific consensus statement on the management of CHB: a 2008 update” [27]; patients taking entecavir dispersible tablets may also be included. (This study will enroll patients who have taken entecavir previously; conversely, patients who have taken immune stimulatory drugs or other antiviral drugs within 3 months will not be enrolled.); (3) patients between 18 to 65 years old; (4) patients showing syndromes of liver stagnation and spleen deficiency and dampness in TCM. For the TCM diagnostic criteria, we refer to “National Standards for TCM Clinical Diagnosis and Treatment in the People’s Republic of China” [28] and the “Medical Consensus of diagnosis and treatment of cirrhosis with integrated TCM and Western medicine” [29], published by the Digestive System Diseases Committee, Society of Integrated Traditional Chinese and Western Medicine.

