#### Modifications

If a patient shows abnormal liver function (such as ALT > 2*ULN) during the trial, this should prompt temporary or permanent cessation of treatment, and the investigator can add hepatoprotective drugs such as silibinin and/or other drugs according to the patient’s condition. At the same time, the researchers will record and follow up the situation of the patient closely. If the patient’s ALT returns to normal after liver protection treatment, with normal values for direct bilirubin and international normalized ratio (INR) at the same time, then he/she may have a chance to continue the trial; otherwise, the patient will stop the trial permanently for safety reasons. If the following conditions occur, subjects should discontinue the trial: (1) poor compliance, irregularly taking medicine, failure to revisit or revisit on time; (2) some combined diseases or complications, or deterioration during the trial; (3) subject self-withdrawal; (4) combining trial drug with other drugs, or not taking test drugs according to research regulations; (5) lost contact; (6) cannot provide complete information.

We also list the following specific stopping criteria. (1) Serious safety problems occur during the test; then the test should be stopped in a timely manner. (2) The drug is found to have no clinical value during the trial; then the trial should be stopped to avoid delaying the effective treatment of subjects. (3) It is found during the trial that there is a major error in the clinical trial protocol and it is difficult to evaluate the effect of the drug; or there is a well-designed protocol with important deviations in the implementation, and it is difficult to continue to evaluate the efficacy and safety of the drug. (4) The sponsor requests to stop the trial (for funding reasons, management reasons, etc.). (5) The State Food and Drug Administration of China orders the trial to be stopped for some reason. (6) The test is suspended due to *force majeure* reasons.

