#### Concomitant care

Other antiviral medicines, such as tenofovir or lamivudine, must not be taken during the trial. If non-antiviral medicines are combined, they will be recorded in the case report form (CRF). If the subjects need other treatment or concomitant care, they should contact the doctor in advance.

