#### Analysis population and missing data

We will use three methods for statistical analysis of the data:
Full analysis set (FAS). According to the intention-to-treat (ITT) principle, all randomized subjects’ data will enter the FAS. For subjects who withdraw from the study early for various reasons, the missing data will be imputed using the method of last observation carried forward (LOCF).Per protocol set (PPS). The study’s PPS will consist of the indicator data for those who enter the study and complete treatment and follow-up, whose medication compliance is 80–120%, who took no combined medication that affected the effectiveness evaluation during the study period, and who have complete evaluation index data and no major test protocol violations.Safety set (SS). The SS includes those subjects who received at least one treatment after randomization.

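### Discontinuation item (4) takes patients out of the trial for combining trial drug with any other drug, while the concomitant-care rule bans only other antivirals; followed literally, it loses cirrhosis assessments that LOCF then scores as event-free

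*Protocol article*

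**What the plan says.** Three sections of the protocol article deal with other drugs taken during the trial.

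- **Modifications.** Six conditions are listed on which subjects should discontinue the trial itself, not only the study drug. Item (4) is "combining trial drug with other drugs, or not taking test drugs according to research regulations". Earlier in the same section, for a patient with abnormal liver function, treatment is stopped temporarily or permanently and "the investigator can add hepatoprotective drugs such as silibinin and/or other drugs". If ALT, direct bilirubin and INR are then normal, "then he/she may have a chance to continue the trial".
- **Concomitant care.** The ban is confined to one class: "Other antiviral medicines, such as tenofovir or lamivudine, must not be taken during the trial". For everything else: "If non-antiviral medicines are combined, they will be recorded in the case report form (CRF". Subjects who need other treatment are asked to contact the doctor in advance.
- **Analysis population and missing data.** The per-protocol set is limited, among other criteria, to patients "who took no combined medication that affected the effectiveness evaluation during the study period". The full analysis set holds all randomized subjects, and for early withdrawals "the missing data will be imputed using the method of last observation carried forward (LOCF").

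Two further sections fix the consequence. The Exclusion criteria bar patients with cirrhosis. The Primary outcome section assesses cirrhosis before treatment, at week 52, and at the follow-up visit 52 ± 2 weeks later.

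**The concern.** Item (4) and the Concomitant care section give opposite instructions for the same patient. Someone who takes a routine non-antiviral alongside trial drug is to be documented and kept under one rule and taken out of the trial under the other.

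This matters because the choice is made at the site while the trial is running. A cirrhosis assessment that is never made cannot be recovered by any later analysis. The missing value is filled by carrying the last one forward, and for this endpoint the last value is the cirrhosis-free status required at entry.

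**Working it through.** **1. The rules side by side, for a patient on trial drug who takes a non-antiviral medicine**

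| Section | Instruction |
|---|---|
| Modifications, item (4) | Leaves the trial; any other drug qualifies |
| Concomitant care | Not banned; recorded in the CRF |
| Per-protocol set | Excluded only if the drug affected the effectiveness evaluation |
| Modifications, liver-function rule | Liver-protecting or other drugs may be added, and the patient may later continue |

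The first two rows conflict directly. The third fits poorly with item (4): completing treatment and follow-up is a separate per-protocol criterion, so a medication criterion would have little to do if every user of another drug had already left. The fourth conflicts only if the added drug is still being taken when trial drug restarts. While treatment is stopped for rescue, nothing is being combined with trial drug.

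**2. From removal to a scored outcome**

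- Status at entry: no cirrhosis (Exclusion criteria).
- Next cirrhosis assessment: week 52 (Primary outcome). Treatment also lasts 52 weeks, so drugs combined with trial drug arise in the interval before that assessment.
- Rule for early withdrawal: LOCF, with the patient kept in the full analysis set.
- Result: a patient removed before week 52 without an exit examination is scored cirrhosis-free, whatever happens later.

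**3. The plan's own figure**

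The Sample size section uses n = (1.96 + 1.282)² / [2(sin⁻¹√0.01 − sin⁻¹√0.05)²] = 334.5, stated as 334 per group. Then 334 × 1.2 × 2 = 801.6, stated as 802, or 401 per group. Both reproduce. They supply the rates and group size used below and are not in dispute here.

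**4. Illustration of the dilution**

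Let w be the share of each arm removed under item (4) before week 52 and carried forward as cirrhosis-free. The document gives no value for w, so 0 to 30% is an assumed range. Assume also that w is equal in both arms, that removed patients have the same underlying risk as the others, and that there are no other losses. The group size stays at n = 401 because removed patients remain in the full analysis set.

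Scored rates: p₁ = 0.05(1 − w) for control and p₂ = 0.01(1 − w) for YQSH.

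Power for the two-proportion (χ²) comparison, with p̄ = (p₁ + p₂)/2: Φ{[(p₁ − p₂) − 1.96√(2p̄(1 − p̄)/n)] / √([p₁(1 − p₁) + p₂(1 − p₂)]/n)}.

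Power on the plan's arcsine scale: Φ{|sin⁻¹√p₁ − sin⁻¹√p₂|√(2n) − 1.96}.

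| w | Control | YQSH | Difference (points) | Power, χ² | Power, arcsine |
|---|---|---|---|---|---|
| 0 | 5.0% | 1.0% | 4.0 | 91.5% | 94.4% |
| 10% | 4.5% | 0.9% | 3.6 | 88.3% | 92.0% |
| 20% | 4.0% | 0.8% | 3.2 | 84.3% | 88.6% |
| 30% | 3.5% | 0.7% | 2.8 | 79.1% | 84.1% |

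The table shows the mechanism. It does not estimate what will happen in this trial.

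**The case against.** The strongest reply is that the document supplies the missing limit. The Concomitant care section is the specific rule on other drugs, the liver-function rule tolerates added drugs, and item (4) pairs other drugs with failure to take trial drug as required. It therefore reads as a protocol-violation clause, and a sensible site would apply it only to prohibited drugs. That may well be the intent. But the text does not say so: the words about research regulations follow the word or, and attach to not taking trial drug. The fix makes the sensible reading the written one.

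It can also be said that the Concomitant care section never states that users of non-antivirals stay in, and that the per-protocol criteria overlap anyway. This is fair as far as it goes. The per-protocol wording is supporting evidence only. The direct conflict is between item (4) and the Concomitant care section.

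A third reply is that LOCF scores every early exit in this way, whatever the reason. That is true. What is particular to item (4) is that the protocol itself would cause exits that its own concomitant-care rule does not call for. The article may also leave an exit examination to the full protocol, which is why the consequence is stated only for patients who have none. The Adherence and Data collection sections keep non-completers' data in the efficacy statistics, but they do not provide for outcome visits after exit.

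A reader might infer more than the document supports:

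- *Observed outcomes are overwritten.* They are not. LOCF fills missing values; the loss is of outcomes that could have been observed.
- *The comparison is biased towards one arm.* Sites and subjects are blinded. Bias would need drug use or removal to differ between arms, and nothing in the document shows that.
- *Removals use up the attrition allowance of 401 − 334 = 67 per arm.* Removed patients stay in the full analysis set, so that allowance does not measure this harm.
- *Herbal medicines and immune stimulants are already prohibited on trial.* The document bars them only as prior treatment. For example, "patients who have taken immune stimulatory drugs or other antiviral drugs within 3 months will not be enrolled" is an entry rule, and the Concomitant care section names neither.

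**Conclusion.** The conflict stands in the current text, and it is minor. Item (4) names no drug class and ends trial participation; the Concomitant care section bans other antivirals only.

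The harm depends on two conditions: that sites apply item (4) literally, and that patients removed before week 52 have no exit examination. Under both, these patients are scored cirrhosis-free and the event rates shrink in proportion to the share removed, even with balanced removal. The actual size cannot be computed, because the document gives no rate of concomitant drug use or of rescue treatment. No between-arm bias is shown.

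**What to change.** Reword item (4) and add one sentence.

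- Limit item (4) to medicines prohibited during the trial: other antivirals, as in the Concomitant care section, plus any further class the sponsor chooses to name. Whether herbal medicines or immune stimulants belong on that list is the sponsor's decision.
- Make item (4) a reason to stop trial drug, not to leave the trial.
- State that patients who stop trial drug still attend the scheduled week 52 and follow-up outcome visits unless they withdraw consent.

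The analysis-set definitions can stay as they are. The cost is a few more visits, already in the schedule, for patients who are off trial drug. Outcomes observed in retained patients will include any effect of the other medicine; the per-protocol criterion already sets aside medicines that affected the effectiveness evaluation.

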#### Adherence

The study will be regularly monitored by a Clinical Research Associate (CRA) in accordance with the corresponding standard operating procedure. The CRA will help ensure that the research center adheres to the research protocol, arranges the supply of research drugs, and ensures that the drugs are kept under appropriate conditions in accordance with instructions. At the beginning of the trial, the researcher would emphasize the importance of compliance to the subjects, and require the subjects to bring back the drug packages (regardless of the remaining drugs) when they visit the research center. At the same time, we will establish an online platform to make immediate contact with the patients, and contact them at least twice a month to learn the patients’ situations and remind them to actively return to the clinic. For those patients who participated effectively during the treatment but could not complete the entire course, and those lost to follow-up, these data will be included in the efficacy statistics and should be analyzed intentionally.

#### Concomitant care

Other antiviral medicines, such as tenofovir or lamivudine, must not be taken during the trial. If non-antiviral medicines are combined, they will be recorded in the case report form (CRF). If the subjects need other treatment or concomitant care, they should contact the doctor in advance.

### Outcomes

#### Primary outcome

The primary outcome is the annual incidence of cirrhosis (the examination methods include instantaneous liver elastic hardness test, abdominal B-mode ultrasound test, or abdominal MRI/CT imaging).

The primary outcome is evaluated before the treatment, at 52 weeks of treatment, and at the 52 ± 2 weeks follow-up visit.

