#### Exclusion criteria

The exclusion criteria are as follows: (1) patients with cirrhosis; (2) patients with liver cancer; (3) patients in acute and chronic hepatitis with non-HBV infection, autoimmune hepatitis, primary biliary cirrhosis, primary sclerosis cholangitis, inherited metabolic liver disease, drug or toxic hepatitis, or alcoholic liver disease; (4) pregnant or lactating women or women planning to become pregnant during the study period; (5) patients who are allergic to the test drugs; (6) patients who have mental disorders and cannot cooperate with the study, or patients with epilepsy in unstable status; (7) patients with severe systemic disease related to the heart, brain, lung, kidney, or hematopoiesis; (8) patients with alcoholism or other unsuitable conditions for enrollment. Patients who are already using TCM will not be enrolled unless they have stopped using TCM for more than 3 months.

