#### Secondary outcomes

The secondary outcomes include HBV DNA negative rate, HBsAg negative rate, HBeAg seroconversion rate, liver function (ALT, aspartate aminotransferase [AST], gamma-glutamyl transferase [GGT], alkaline phosphatase [ALP], serum albumin [ALB], and total bilirubin [TBIL]), spleen thickness, and the evaluation scores of patients’ clinical symptoms.

These indicators are observed before the treatment, at 26 weeks of treatment, at 52 weeks of treatment, at the 26 ± 2 weeks follow-up period, and at the 52 ± 2 weeks follow-up period.

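### A patient who shows cirrhosis at a 26-week visit and leaves before the next annual evaluation can be carried forward as cirrhosis-free

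*Protocol article*

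**What the plan says.** All references are to the protocol article.

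- **Primary outcome.** The outcome is the annual incidence of cirrhosis, and "the examination methods include instantaneous liver elastic hardness test, abdominal B-mode ultrasound test, or abdominal MRI/CT imaging". On timing: "The primary outcome is evaluated before the treatment, at 52 weeks of treatment, and at the 52 ± 2 weeks follow-up visit".
- **Secondary outcomes.** The list includes "spleen thickness, and the evaluation scores of patients’ clinical symptoms". Its schedule is denser: "These indicators are observed before the treatment, at 26 weeks of treatment, at 52 weeks of treatment, at the 26 ± 2 weeks follow-up period", and then the final follow-up visit. No measuring method is given for spleen thickness.
- **Exclusion criteria.** Patients with cirrhosis cannot enter, so every eligible patient has a cirrhosis-free baseline.
- **Modifications.** Among the reasons for which subjects should discontinue is "some combined diseases or complications, or deterioration during the trial".
- **Analysis population and missing data.** All randomized patients enter the full analysis set, and missing data after early withdrawal are imputed by LOCF.
- **Statistics, Outcomes.** The primary comparison is a chi-square test of incidence.
- **Additional analyses.** No sensitivity analysis is planned.

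**The concern.** Each rule is unremarkable alone. Together they can give a wrong result for one kind of patient. Suppose cirrhosis is visible on imaging at week 26 and the patient then leaves, perhaps because the change is judged a deterioration. There is no week-52 evaluation. The only earlier scheduled cirrhosis evaluation is baseline, which is negative by eligibility. LOCF then enters this patient as a non-event. The same happens to a patient who is cirrhosis-free at week 52, shows cirrhosis at follow-up week 26 and leaves before follow-up week 52.

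At stake is a small event count: at the planned rates, about 20 control and 4 YQSH cases in a year. If the same share of early cases is lost from both arms, more are lost from control and the absolute difference shrinks. If the shares differ, the comparison is also distorted by who was withdrawn. With no sensitivity analysis planned, nothing stated in the article would show either effect.

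**Working it through.** **Inputs.** From the Sample size section: control rate 5%, YQSH rate 1%, two-sided alpha 0.05 (1.96), power 90% (1.282), 334 per group before attrition, 20% attrition, 401 per group after. Assumed here: a constant hazard within year 1, and the shares of patients leaving, for which the article gives no figures.

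**1. The plan's own figure.** With the printed arcsine formula, asin√0.05 − asin√0.01 = 0.2255 − 0.1002 = 0.1253. Then n = (1.96 + 1.282)² / (2 × 0.1253²) ≈ 334.5 (computed without rounding), against the stated 334. And 334 × 1.2 × 2 = 801.6, against 802. Both reproduce. By the same approximation, power = Φ(√(2n) × 0.1253 − 1.96), which is 90.0% at 334 per arm and 94.4% at 401.

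**2. Cases by week 26.** P(cirrhosis by week 26) = 1 − (1 − p)^0.5, which is 2.53% for control and 0.50% for YQSH. Times 401, that is 10.2 and 2.0 cases, out of 20.1 and 4.0 by week 52.

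**3. Patients who stay and remain cirrhotic.** All of them are still cirrhotic at week 52 and are counted there. Scoring week 26 adds no case.

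**4. Dropout unrelated to outcome.** Let 20% leave in year 1 (401 × 0.20 = 80.2 per arm), all carried forward as cirrhosis-free. Counted cases are 401 × 0.8 × 0.05 = 16.0 and 401 × 0.8 × 0.01 = 3.2, with power 88.6%. Counting week-26 readings recovers 80.2 × (share leaving after week 26) × P(cirrhosis by week 26):

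| Share of dropouts leaving after week 26 | Control cases recovered | YQSH cases recovered | Power with them counted |
|---|---|---|---|
| 0% | 0 | 0 | 88.6% |
| 50% | 1.0 | 0.2 | 90.5% |
| 100% | 2.0 | 0.4 | 92.0% |

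If the 20% is instead spread evenly over 104 weeks, 401 × 0.20 × 26/104 ≈ 20 patients per arm leave between weeks 26 and 52. That is 20 × 2.53% ≈ 0.5 control and 20 × 0.50% ≈ 0.1 YQSH cases. Losing only those takes power from 94.4% to 93.9%.

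**5. Withdrawal because of the event.** With no other attrition, let a share f of week-26 cases be withdrawn and carried forward as cirrhosis-free. Cases counted are 401p − f × 401 × [1 − (1 − p)^0.5]:

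| f (assumed) | Control cases | YQSH cases | Power, 401 per arm |
|---|---|---|---|
| 0% | 20.1 | 4.0 | 94.4% |
| 10% | 19.0 | 3.8 | 93.3% |
| 25% | 17.5 | 3.5 | 91.1% |
| 50% | 15.0 | 3.0 | 86.3% |
| 100% | 9.9 | 2.0 | 69.3% |

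**The case against.** **Annual visits fit an annual incidence.** This stands. A reader might infer that every case visible at a 26-week visit goes uncounted. The article does not support that: nothing says an earlier case is disregarded, and step 3 shows that persisting cases are picked up at week 52.

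**Imaging at the 26-week visits is not stated.** This also stands as a caution. The article gives no method for spleen thickness, and the schedule figure is not available in the text reviewed. The inference is still strong, because the only abdominal imaging the article names is ultrasound or MRI/CT, and both are endpoint examinations. Whether a spleen measurement also yields an adequate liver reading is open, and elastography is not placed at those visits in the text.

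**The Modifications section does not call new cirrhosis a deterioration.** Correct. The wording allows that reading without requiring it, so a reader should not conclude that the trial withdraws every new case.

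**Other sections may rescue the case.** Adherence and Data collection bring non-completers' data into the efficacy statistics, Formal committee sends main indicators to a clinical endpoint committee, and Harms records all adverse events. None of these makes a 26-week scan a primary-outcome reading or displaces LOCF from baseline.

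**The power losses are assumed.** True. A steeper figure is also tempting: if half of all year-1 events were lost, power at 334 per arm would fall from 90.0% to 62.4%. At constant hazard that needs essentially every early case to be both seen and then lost, so it is a bound and not an expectation.

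**Conclusion.** The point holds in a limited form. Annual-only scoring, discontinuation and LOCF together allow a patient with documented cirrhosis to be analysed as cirrhosis-free, but only if that patient leaves before the next annual evaluation. When leaving is unrelated to outcome the effect is small: 0 to 2.0 control and 0 to 0.4 YQSH cases in year 1. It becomes material only if a good part of the early cases is withdrawn because of the event: power is 91.1% at a quarter, 86.3% at half and 69.3% if all are lost, against 94.4%. These figures rest on a constant hazard, assumed shares, and the inference that imaging at the 26-week visits can show cirrhosis. The planned sample size is not affected. The change is worth making because the rule misclassifies a known event and the correction uses data the trial probably already collects.

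**What to change.** In the Primary outcome section and in Analysis population and missing data, state two things:

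1. Cirrhosis documented on any trial imaging before withdrawal, including at the 26-week visits, and confirmed by the existing clinical endpoint committee, blinded and under the same criteria, counts as a primary event of that year, whether or not the patient stays.
2. For a patient who leaves, the last cirrhosis status is the latest imaging reading, not baseline.

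Keep the annual-incidence endpoint and the chi-square test; a first confirmed positive by week 52 is simply a year-1 case. Reconcile the Modifications and Primary outcome sections on whether a patient who reaches the primary endpoint is still followed for outcome.

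The cost is protocol wording, a case report form field and a few extra committee reads. If spleen thickness is imaged as inferred, no new procedure is needed. The downside is that ultrasound-only readings may be less accurate than visits with elastography, which is why committee confirmation under the same criteria is part of the rule.
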